***Primary outcomes***	
Housing status	Housing status is measured using questions from the Los Angeles County Homeless Count demographic survey [51]. Participants are asked, “In the past 30 days, please indicate all places where you have slept for at least one night.” Response options include (1) My own apartment or home; (2) Someone else’s apartment or home; (3) In a shelter, emergency, temporary housing; (4) Hotel/motel provided by an agency; (5) Outside on the street, park, or beach; (6) Tent or makeshift shelter; (7) In a bus station, train station, airport; Abandoned building; (8) In a vehicle (car, van, RV, truck); (10) An institution, hospital, or facility. A follow-up question could include, “If you stayed in more than one place, where did you stay the most?” Participants are also asked up to three possible questions with “yes” or “no” as response options. These include: Do you currently have a case worker who can help you with housing assistance? Do you currently have a housing assistance voucher? Are you on a waitlist for housing assistance?
Loneliness	UCLA Loneliness Short Version is a validated instrument [52] that measures three dimensions of loneliness: relational connectedness, social connectedness, and self-perceived isolation. Participants are asked three questions: (1) How often do you feel that you lack companionship? (2) How often do you feel left out? (3) How often do you feel isolated from others? Response options include: Hardly ever; Some of the time; Often
Social support	The Oslo Social Support Scale is a 3-item self-report measure of the level of social support [53]. Participants are asked three questions with different response options. The first is: “How many people are so close to you that you can count on them if you have great personal problems?” with response options of: None; 1–2; 3–5; or 5 + . The second is: “How much interest and concern do people show in what you do?” with response options of: None; Little; Uncertain; Some, or A lot. The third is: “How easy is it to get practical help from neighbors if you should need it?” with response options of: Very difficult; Difficult; Possible; Easy; or Very easy
***Other covariates***	
Demographic and historic information (baseline only)	The baseline survey includes questions about the following demographic and historic information taken from previous research studies related to homelessness: age, sex, gender, sexual orientation, race and ethnicity, country of origin, relationship status, children, level of education, military service, health insurance, public benefits, employment, monthly income, criminal justice involvement, homeless history, housing preferences, and health conditions
Employment status	Employment status is measured using questions from the Los Angeles County Homeless Count demographic survey [51]. Participants are asked, “What is your employment status?” with the following response options: Employed, full-time (35 h a week or more); Employed, part-time; Unemployed, looking for work; Unemployed, not looking for work; Retired, receiving retirement benefits; and Retired, not receiving benefits. Participants are also asked to indicate their total monthly income
Financial well-being	Adapted questions from the Consumer Finance Protection Bureau’s abbreviated 5-item measure are used. Questions include: “Usually, do you have enough money to meet your needs?” with response options: Completely; Mostly; Moderately, A little; Not at all. “How often (always, often, sometimes, rarely, never) does this statement apply to you? (1) I have money left over at the end of the month; and (2) My finances control my life.” “How well (completely, very well, somewhat, very little, not at all) do the following statements describe you or your situation? (1) Because of my money situation, I feel like I will never have the things I want in life; (2) I am just getting by financially; and (3) I am concerned that the money I have or will save won’t last.” Participants are also asked if and what health insurance they have; monthly benefits that they receive (e.g., general relief, social security disability income or Supplemental Security Income; Supplemental Nutritional Assistance); if they have a bank account; and whether they were able to pay all bills last month
Food security	Two items taken from United States Department of Agriculture Household Food Security Survey ask about how often it is usually true for the participant (“often,” “sometimes,” “never,” or “I don’t know”) in the past 30 days: “I worry whether my food will run out before I get money to buy more” and “The food I bought just doesn’t last and I don’t have money to get more.”
Life satisfaction	General life satisfaction is assessed using a 7-item validated measure from the World Health Organization Quality of Life toolkit [54]. Questions include: In general, how satisfied are you with your life? How satisfied are you with your ability to perform your daily living activities? How satisfied are you with your personal relationships? How satisfied are you with the support you get from your friends and family? How satisfied are you with your ability to provide for or support others? How satisfied are you with the way you spend your time? How would you rate your quality of life? Response options for all questions are: Very satisfied; Satisfied; Neither satisfied nor dissatisfied; Dissatisfied; Very dissatisfied
Physical health	The PROMIS Global Health Scale Version 1.2 (2 items, self-rated physical health and activities) is used: “In general, how would you rate your physical health?” Response options: Excellent; Very good; Good; Fair; Poor. “To what extent are you able to carry out your everyday physical activities such as walking, climbing stairs, carrying groceries, or moving a chair?” Response options: Completely; Mostly, Moderately; A little; Not at all
Mental health	PROMIS is also used to assess mental health (2 items, self-rated mental health, frequency bothered by symptoms): “In general, how would you rate your mental health, including your mood and your ability to think?” Response options: Excellent; Very good; Good; Fair; Poor. “In the past 7 days, how often have you been bothered by emotional problems such as feeling anxious, depressed, or irritable?” Response options: None at all; A little; A moderate amount; Very much; An extreme amount
Social health	PROMIS is used to assess social health (1 item, self-rated satisfaction with social activities and relationships): “In general, please rate how well you carry out your usual social activities and roles (this includes activities at home, at work, and in your community, and your responsibilities as a parent, child, spouse, employee, friend, etc.).” Response options: Excellent; Very good; Good; Fair; Poor
Substance use	Participants are asked: In the last month, how often did you: (1) have a drink containing alcohol? (2) take substances like cannabis/marijuana, meth, cocaine, fentanyl, heroin, prescription opioids, etc.? Response options include: Never; once or twice; Once a week; 2 to 3 times a week; 4 to 6 times a week; Daily; Prefer not to answer. Participants are also asked if they are currently receiving treatment for substance use (including alcohol) and how much money in the past month that they have spent on (1) Cigarettes and (2) drugs and alcohol
Sleep	Sleep disturbance is measured using two questions from the WHO Quality Of Life Scale [54]: Do you have any difficulties with sleeping? How much do sleep problems worry you? Response options: None, A little, A moderate amount; Very much; An extreme amount
Psychological distress	Via the Kessler Psychological Distress Scale [55], participants are asked how often over the past month that they have had certain feelings on a scale of: None of the time; A little of the time; Some of the time; Most of the time; All of the time. Feelings include: Tired out for no good reason; Nervous; So nervous that nothing could calm you down; Hopeless; Restless or fidgety; So restless you could not sit still; Depressed; That everything was an effort; So sad that nothing could cheer you up; and Worthless
Health care utilization	Participants are asked how many times they have seen a doctor or health care provider for nonemergency care in the past 30 days
Criminal justice involvement	Participants were asked: In the past 3 months, have you had contact with the police? In the past 3 months, how many times have you been arrested? Did a new arrest lead to new charges pending against you? During the past 3 months, did you stay one or more nights in prison or jail?
Perceived discrimination	A short version of the daily discrimination subscale includes six items and attributions for why a person experienced discrimination. Items regarding discrimination include: You are treated with less courtesy than other people; You receive poorer service than other people at restaurants or stores; People act as if they think you are not smart; People act as if they are afraid of you; You are followed around in stores; You are threatened or harassed. Response options are: Often; Sometimes; Rarely; Never. Participants who have perceive discrimination are asked, “What do you think is the main reasons for these experiences?” and can check all that apply: (1) Your ancestry or national origins; (2) Your gender; (3) Your race; (4) Your religion; (5) Your weight/height; (6) Some other aspect of your physical appearance; (7) Your sexual orientation; (8) Your education or income level; (9) Your housing status

At the end of each survey, participants are asked two open-ended questions: (1) Looking back over the last 3 months, what do you think was the most significant change to your quality of life? (2) Tell me in a sentence or two, what are your most important goals in life right now? If the survey is administered by a surveyor, responses are entered verbatim as much as possible; if self-administered, participants enter their responses directly. All surveyors complete a training on best practices for trauma-informed interviewing.

### Qualitative data collection procedures

#### Miracle money recipients

Qualitative interviews will be conducted in English with a subset of 20 participants who receive basic income—shortly after receipt of the first of 12 monthly payments and again around the time of their last payment. During the first quarterly survey, participants who received monthly income will be purposively sampled and asked if they would be interested in participating in an additional in-depth qualitative interview to learn more about their experience with the program. Maximum variation sampling will be used to ensure differences in race, ethnicity, and gender in our qualitative subsample. Those who are interested and agree to participate will be contacted by a research team member who has been trained in conducting qualitative interviews. Interviewers will schedule a convenient time and place to meet unless participants request a phone interview. Once an addendum consent is completed, semistructured interviews will last between 30 and 60 min and include questions about how participants view their lives, general experiences with the Miracle Friends program, and the Miracle Money program, including how they use the money and any difference it has made in their lives. Interviews will be audio recorded and transcribed verbatim.

#### Miracle friend volunteers

A single qualitative interview will be conducted with 20 volunteers who served as a phone buddy for at least 6 months to understand their experience of Miracle Friends. Any volunteer who has been engaged in the intervention for at least 6 months will receive an email from the Miracle Messages program that informs them of the study and refers them to the study team if they are interested in speaking about their personal experience with the program. Thirty-three volunteers have indicated that they would be interested; 20 have been purposively sampled to include volunteers who had participants in the Miracle Friends program and Miracle Money program. Phone or videoconferencing interviews have been conducted using a semistructured interview guide that included questions about how and why participants became a volunteer, experiences with the program, and whether they felt that they had an impact on their unhoused friend or if their friend has affected their life. Questions about how the program could be improved were also included. Interviews have typically lasted between 25 and 35 min and were audio recorded and transcribed verbatim. Written informed consent has been waived by the institutional review board for volunteer interviews.

### Quantitative data analysis

#### Social isolation outcomes

To evaluate the efficacy of the Miracle Friends intervention on social support, psychological distress, and loneliness, we will use responses to the Oslo Support Scale [53], Kessler Psychological Distress Scale [55], and UCLA Loneliness Scale [52], respectively, at the final survey (Quarter 5). Each measure will first be summed to develop a total score, then dichotomized based on cutoffs for each measure based in the literature—i.e., poor social support will be coded as 1 if the Oslo Support Scale sum score is less than 9 (indicative of poor social support) and 0 otherwise; psychological distress will be coded as 1 if the Kessler Psychological Distress Scale sum score is greater than 25 (indicative of high psychological distress) and 0 otherwise; and loneliness will be coded as 1 if the UCLA Loneliness Scale sum score is greater than or equal to 6 (indicative of high loneliness) and 0 otherwise. Each dichotomized score will be modeled as a function of treatment group (1 = Miracle Friends or Miracle Money group members who participated in at least one phone buddy intervention, 0 = waitlist group); covariates including demographic characteristics, physical and mental health, and substance use; and a random intercept for city in random intercept logistic regression models.

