Regardless of group assignment, all participants identified by a unique study identification number to preserve confidentiality have been asked to complete a baseline survey and five subsequent quarterly surveys; participants will receive a $30 gift card incentive for each completed survey. Qualitative interviews with a subset of 20 participants receiving basic income have and will be conducted shortly after receipt of the first of 12 monthly payments, with another follow-up qualitative interview scheduled around the time of the last payment. A single qualitative interview will be conducted with 20 volunteers serving as a phone buddy for at least 6 months to understand their experience of delivering the Miracle Friends intervention. Participants will receive a $30 incentive at the end of each qualitative interview. This human subjects’ research is being performed in accordance with the Declaration of Helsinki with protocols approved by the first author’s institutional review board. Reporting of study protocols follows the SPIRIT guidelines [47], which include a schedule of enrollment, interventions, and assessments, as depicted in Fig. 2. The SPIRIT checklist for Trails can be found in the Supplementary materials.

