### Quantitative data collection procedures

Upon enrollment in the study and regardless of group assignment, the participants complete a baseline survey that takes approximately 45 min and includes questions about demographic characteristics, homelessness history, physical and mental health status, health service utilization, employment, substance use, socioeconomic status, and income. Participants are also asked to provide an email address and collateral contact information for one or more people to ensure that the study team can reconnect with them when it is time to complete a shorter survey five more times, one every 3 months (i.e., quarterly) until 15 months. The quarterly survey asks about similar topics and takes approximately 25 min. Surveys can be completed in person or over the phone, with responses recorded by a surveyor directly into the REDCap data management platform [49, 50] that is also used to support data visualization to monitor data quality and study retention. Upon request, participants also receive a link to self-administer the survey in English or Spanish. Table 1 describes all study measures.

**Table 1 Tab1:** Study measures and scales

Measure	Description

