#### Statistical power

To reach a target goal of 105 participants receiving basic income through Miracle Money, recruitment efforts have yielded more than 200 individuals in each treatment group. Assuming that each arm will have at least 105 participants, our study can detect the hypothesized 50% difference in proportion of people exiting homelessness at Quarter 5 between the Miracle Money and waitlist group (assuming 60% of the Miracle Money group exits homelessness and 10% of the waitlist group exits homelessness) using a *p*-value threshold of 0.05 with power exceeding 95%. When comparing the Miracle Friends group to the waitlist group, our study can detect the hypothesized 15% difference in proportion of people exiting homelessness at Quarter 5 between the Miracle Friends and waitlist group (assuming 25% of the Miracle Money group exits homelessness and 10% of the waitlist group exits homelessness) using a *p*-value threshold of 0.05 with power exceeding 60%. Differences in proportions of the social isolation outcomes will be detected at powers identical to the housing outcome, assuming identical differences in proportions and *p*-values. Regarding the effect modification of treatment by race in exiting homelessness, our study will be able to detect a difference in proportion of groups exiting homelessness of 35% with power exceeding 20%. Main effect calculations were done on unadjusted models using the WebPower R package, and the effect modification power calculations were performed via simulation.

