### Trial status

This version of the study protocols (2.1) includes two amendments to the initial protocols approved by the institutional review board on April 21, 2022. Recruitment began on May 30, 2022, and ended July 10, 2023. Final enrollment into the Miracle Money intervention was delayed until August 2023 to give study participants an opportunity to meet the criterion for receiving basic income (i.e., participating in the Miracle Friends program).

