### Limitations

This study is unique in that it represents the first known experiment of interventions that provide social support and guaranteed income for PEH. Challenges include study retention, given that participants have been recruited while experiencing homelessness, either sheltered or unsheltered. There may also be differential retention rates because people receiving basic income may be more likely to complete follow-up surveys as compared to the waitlist or Miracle Friends only groups. The likelihood that unhoused participants continue with the program may depend on the type of volunteer match they receive, including concordance between the two parties based on factors such as race, ethnicity, age, or gender, which this study will not examine because we have not captured dyadic information. The study also will not follow people after the basic income funding has ended. It should also be noted that this intervention primarily focused on individuals who had a cell phone, which research suggests is much of the homeless population [57].

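### The stated outcome models use only the Quarter 5 survey and leave Quarters 1–4 unused; the Limitations also wrongly say that no one is followed after payments end

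*Protocol article*

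**What the plan says.** All participants "have been asked to complete a baseline survey and five subsequent quarterly surveys", spaced "one every 3 months (i.e., quarterly) until 15 months" (Design overview; Quantitative data collection procedures).

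Under Social isolation outcomes, social support, psychological distress and loneliness are taken "at the final survey (Quarter 5"), dichotomized, and modeled on treatment group, covariates and "a random intercept for city in random intercept logistic regression models". Neither a participant effect nor a visit term appears. Housing outcomes uses the same model form without naming a time point. Statistical power supplies one, referring to the "proportion of people exiting homelessness at Quarter 5 between the Miracle Friends and waitlist group".

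Limitations contains two relevant sentences. One says "There may also be differential retention rates because people receiving basic income may be more likely to complete follow-up surveys", compared with the waitlist and Miracle Friends only groups. The other says "The study also will not follow people after the basic income funding has ended".

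Under Miracle Money, payments run for 12 months and begin only after a match and at least two contacts within a month, so the start date differs between people. Trial status adds that "Final enrollment into the Miracle Money intervention was delayed until August 2023".

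**The concern.** The trial collects five follow-up measurements, and its stated outcome models use one. Someone who answered Quarters 1–4 and missed Quarter 5 has four informative responses, and none enters the model as written. This population is hard to reach: Results already reports 103 people who could not be contacted after assignment. The authors themselves raise unequal retention as a possibility.

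Two things are at stake. The first is precision. The second is bias, if those missing at Quarter 5 differ in their earlier outcomes and this pattern is not the same in the two groups compared.

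A related problem is what Quarter 5 means for people receiving income. Survey time runs from enrollment and payment time from verified participation. At month 15 a recipient may be still in payment or finished, and the article's statement about follow-up after funding does not fit its own schedule.

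**Working it through.** **1. Surveys used.** Five follow-up surveys less the one analyzed leaves four outside every stated outcome model.

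**2. Precision, on the plan's own scenario.** Inputs from Statistical power: 105 per arm, 25% versus 10%, threshold 0.05 (taken as two-sided). With p̄ the pooled proportion,

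power = Φ{[0.15 − 1.96·√(p̄(1−p̄)(1/n₁+1/n₂))] / √(0.1875/n₁ + 0.09/n₂)}.

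With n₁ = n₂ = 105 and p̄ = 0.175 this is Φ[(0.15 − 0.103)/0.0514] = 0.82 (0.83 by the arcsine method). The article says only that power exceeds 60%. That holds as a lower bound, and the gap is a separate matter. Retention is not reported, so the rates below are assumed:

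| Quarter 5 retention, treated / waitlist | Analyzed | Power (pooled / arcsine) |
|---|---|---|
| 100% / 100% | 105 / 105 | 0.82 / 0.83 |
| 80% / 80% | 84 / 84 | 0.73 / 0.74 |
| 80% / 60% | 84 / 63 | 0.65 / 0.68 |
| 70% / 50% | 73.5 / 52.5 | 0.57 / 0.61 |

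These figures apply only if 105 counts people before dropout. More than 200 were randomized to each arm, so the real loss may be smaller. A longitudinal model would recover part of it, depending on how strongly the surveys correlate.

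**3. Dropout by arm alone.** Let p be the true proportion with the outcome, and r₁ and r₀ the retention of those with and without it. If missing people are simply left out,

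observed proportion = p·r₁ / [p·r₁ + (1−p)·r₀].

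Take p = 0.20 in both arms. With treated retention 85% and waitlist retention 60%, both unrelated to outcome, each arm shows 0.200 and the difference is 0. More generally, the observed odds ratio is the true odds ratio times the ratio of r₁/r₀ between arms. It is distorted only when that ratio differs by arm.

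**4. Dropout by arm and by the Quarter 5 outcome itself.** Assume no true effect, treated retention 80% throughout, and outcome-related retention in the waitlist only.

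- p = 0.20, waitlist retention 70% with the outcome and 55% without: 0.14/(0.14+0.44) = 0.241, difference −4.1 points.
- Pattern reversed: 0.11/(0.11+0.56) = 0.164, difference +3.6 points.
- p = 0.30: 0.21/(0.21+0.385) = 0.353 and 0.165/(0.165+0.49) = 0.252, differences −5.3 and +4.8 points.

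This is missing-not-at-random, so a longitudinal model alone does not cure it.

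**5. Dropout by arm and by an earlier outcome.** Now attach the same retention rates to status at Quarter 4, with 20% positive then. Let a and b be the chances of the outcome at Quarter 5 for people positive and negative at Quarter 4. The observed waitlist proportion shifts by (a − b) times the shift in step 4. With a − b between 0 and 1, the spurious difference lies between 0 and −4.1 points, or between 0 and +3.6 points for the reverse pattern. A model containing Quarter 4 can remove this part.

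**6. Payment timing.** With a first payment L months after enrollment, the paid period ends at month L + 12, which is L − 3 months relative to Quarter 5:

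| L (months) | 1 | 2 | 3 | 4 | 6 |
|---|---|---|---|---|---|
| End of paid period relative to Quarter 5 | −2 | −1 | 0 | +1 | +3 |

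The last person enrolled (10 July 2023) reaches Quarter 5 about 10 October 2024. If that person was paid at all, the first payment came by August 2023, reading final enrollment into Miracle Money as the last payment start. The twelfth payment then fell by July 2024, about three months before the survey. The section on qualitative interviews with recipients also plans to sample people already receiving income at the first quarterly survey, so starts within three months are foreseen.

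**The case against.** The strongest reply is that a single prespecified endpoint is an ordinary choice, the article is a condensed account, and missing-data handling may sit in an analysis plan that is not shown. All of that stands. Silence on imputation or weighting is not the criticism. What is open to criticism is the stated model, which has no place for Quarters 1–4.

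A reader might infer several stronger things that the documents do not support:

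- **That unequal retention by itself biases the comparison by 4 to 5 points.** Step 3 gives zero. The larger figures need an assumed interaction between arm and outcome, and their sign reverses with the assumption. The article says only that retention may differ.
- **That non-responders will be discarded by rule.** The article states no such rule; this follows only from fitting the model as written.
- **That the illustration applies directly to housing.** The Housing outcomes section compares Miracle Friends participants with the waitlist, and the retention remark puts both of those groups on the same side, against income recipients. The remark bears on the social isolation models, which include Miracle Money members in the treated group.
- **That recipients at Quarter 5 range from no payments to all 12.** The dates permit someone enrolled 30 May 2022 to be first paid in August 2023, with 0 or 1 payments by Quarter 5 (about 30 August 2023). Nothing says this happened, and no distribution of start dates is given.

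The Limitations sentence might be read as meaning only that there is no follow-up after the program as a whole is funded. Step 6 conflicts with that too: 12 payments from the last starts in August 2023 end by July 2024, and the last surveys fall about October 2024.

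**Conclusion.** The point holds as a recommended improvement, not as an error in the choice of endpoint. The social isolation models use Quarter 5 only, and the housing model apparently does so too, on the strength of the power section. Four collected surveys contribute nothing to any stated outcome model. The cost is lost precision, plus bias if dropout depends on arm together with earlier outcomes. Under the assumed rates in step 5 that bias is 0 to about 4 points in either direction, against a hypothesized Miracle Friends effect of 15 points. Its true size and direction cannot be known without retention data.

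Two smaller conclusions follow from the schedule. Payment status at Quarter 5 can be ongoing or ended, in proportions not reported. And the statement that people are not followed after funding contradicts a 12-month payment period inside a 15-month follow-up, for anyone first paid within about three months of enrollment.

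**What to change.** 1. Fit one longitudinal logistic model per outcome to all five quarterly surveys, with assigned arm by visit, the baseline value of the outcome, the planned covariates, and within-participant correlation. The baseline value matters mainly for the three scales, since everyone was homeless at entry.
2. Keep the Quarter 5 contrast as primary, reported as a marginal risk difference or odds ratio so that its meaning does not depend on the random-effects structure.
3. Add a delta-adjusted (tipping-point) sensitivity analysis for missing-not-at-random dropout, which the longitudinal model does not address, and report retention by arm and survey.
4. Describe Miracle Money recipients' payment status (before, during or after payments) at each survey.
5. Correct the Limitations sentence: those first paid within about three months of enrollment are surveyed at Quarter 5 after their last payment.

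The cost is analysis-plan wording and modest extra programming. The surveys are already scheduled, and payment dates should be available from the program's payment records. The main analysis would then rely on missing-at-random, and the plan should say so.
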